### Interventions

The eight subdistricts are manually grouped into homogenous pairs with regard to community socioeconomic status and land mix use. From these pairs, one intervention subdistrict is randomly chosen, the remainder serves as control subdistrict.

A physical activity program tailored to the specific situation in the respective subdistrict will be developed in each of the intervention subdistricts with active involvement of the general public and other stakeholders. For tailoring, data from situational analysis, baseline surveys, and participatory actions (community forum, workshops, and excursions) is used. Each development step is communicated and discussed in the community and tested for its feasibility. The intervention material is being developed as part of an ecological model [16]. Implementation will be done with the help of local stakeholders and key actors of the population to ensure sustainability. A community round table with all stakeholders will take place throughout the intervention phase in the intervention subdistricts.

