### Outcomes

For the formal CRT evaluation, baseline and follow up surveys are carried out in the eight study subdistricts. These include 7-days measurements of physical activity (3D accelerometer, ActiGraph, Pensacola (FL)) and fitness (modified Senior Fitness Test [29]) a short physical examination (blood pressure, short anthropometry) and a self-administered questionnaire on intrapersonal, interpersonal, and environmental determinants of physical activity. Training sessions on fitness test and physical examination are held regularly for the field staff to ensure standardised measurements.

The primary outcome is amount of PA measured by accelerometer in average counts per minutes (CPM). The secondary outcome is physical fitness. The tests are handgrip strength, chair stand, 2-min step, back scratch, sit and reach, and flamingo balance test. Further secondary outcomes are time spent outdoors in minutes per day (measured by questionnaire) and inactivity in hours per day (measured by questionnaire). The impact evaluation will include identified key determinants. Evaluation of efficacy and possible adverse effects of the PA promotion will be done stratified by sex. Mixed models will be used to account for the clustered structure of the data introduced by the two-stage sampling design.

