**Fig. 2 Fig2:**
[figure not shown]
Timeline of the OUTDOOR ACTIVE intervention trial

The sample size calculation is based on data gathered during the OUTDOOR ACTIVE pilot study. Accelerometer-based average counts per minute (CPM) will be used for evaluation. Mean CPM ranged from 1587.5 (SD 470.7) to 1697.0 (SD 440.5) in the five highly heterogeneous subdistricts (ICC = 0.0024). CPM were consistently higher in women than in men with only moderate differences for SES. In the OUTDOOR ACTIVE intervention trial, a mean difference of 150 CPM (equivalent to standardized effect size of 0.33) is targeted. Assuming a fixed number of clusters (four intervention, four control), 204 participants will be needed in each study arm (significance level 5% two-sided, power 90%) summing up to 808 for sex-stratified trial evaluation. Assuming a fixed proportion of 30% for dropouts, 144 participants (72 female, 72 male) are needed in each of the subdistricts at baseline.

Since no intervention is developed in the control subdistricts, and active involvement of the study participants is required in the intervention subdistricts, blinding was not a feasible option for the intervention trial. Instead, for communication with the public, the study is separated into two parts: one part containing the surveys (“BUTEN AKTIV Gesundheitsuntersuchung” OUTDOOR ACTIVE health surveys), which take place in all eight subdistricts and focuses on longitudinal aspects of the ageing process; the second part containing the intervention development and implementation, takes only place in the four intervention subdistricts (“BUTEN AKTIV vor Ort” OUTDOOR ACTIVE on-site). Thus, participants of the survey might or might not be aware of the intervention development.

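### The 90% power stated for each sex rests on normal quantiles; with eight randomised subdistricts and a t reference on 6 degrees of freedom it is about 75%

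*Protocol article*

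**What the plan says.** All sources are in the Methods/design part of the Protocol article.

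- **Participant timeline, blinding and sample size** (text after Fig. 2). The target is set as "a mean difference of 150 CPM (equivalent to standardized effect size of 0.33) is targeted". The pilot data are given as "Mean CPM ranged from 1587.5 (SD 470.7) to 1697.0 (SD 440.5") "in the five highly heterogeneous subdistricts (ICC = 0.0024"). The requirement is "Assuming a fixed number of clusters (four intervention, four control), 204 participants will be needed in each study arm" ("significance level 5% two-sided, power 90"%). The total is then about doubled, "summing up to 808 for sex-stratified trial evaluation", so the 204 per arm and the 90% apply within each sex.
- **Interventions.** The eight subdistricts form four pairs, and allocation is within pairs: "From these pairs, one intervention subdistrict is randomly chosen, the remainder serves as control subdistrict".
- **Outcomes.** Efficacy is evaluated by sex, and "Mixed models will be used to account for the clustered structure of the data introduced by the two-stage sampling design". The article does not say which reference distribution or degrees of freedom the mixed model uses, or whether the pairs enter it.

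**The concern.** The treatment effect is a contrast between four intervention and four control subdistricts. Its standard error contains between-subdistrict variance, which must be estimated from those eight units. That leaves 6 degrees of freedom (8 − 2), or 3 if the four pairs are respected (4 − 1). The two-sided 5% critical value is then 2.447 or 3.182, against 1.96 under the normal. Inflating the sample for the ICC corrects the size of the standard error but not the uncertainty in estimating it.

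If the 90% was computed without this, a true effect of 150 CPM would be missed within a given sex in about one trial in four (6 degrees of freedom), not one in ten. A null sex-specific result would then be read as stronger evidence against the intervention than it is.

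**Working it through.** **Inputs from the article:** d = 0.33 (150 CPM, so SD = 150/0.33 = 454.5); pilot SDs 440.5 and 470.7; ICC ρ = 0.0024; k = 4 subdistricts per arm; 204 per arm per sex, so m = 204/4 = 51 per subdistrict; two-sided 5%.

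**1. Reproducing 204.** Unclustered size per arm: n = 2(1.960 + 1.282)²(SD/150)². Inflation for a fixed number of clusters: n·k(1 − ρ)/(k − ρn).

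- SD 440.5, k = 4: n = 181.2, inflated to 202.9. Rounded up to 51 per subdistrict this is 204.
- d = 0.33, k = 4: n = 193.0, inflated to 217.7.
- d = 0.33, k = 8: inflated to 204.3.

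The article does not say which route it took. Both routes that give 204 use normal quantiles.

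**2. Standard error and noncentrality at 204 per arm.**

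SE(d) = √(2[1 + (m − 1)ρ]/204) = √(2 × 1.12/204) = 0.1048

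Noncentrality = 0.33/0.1048 = 3.149

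**3. Power per sex, no baseline adjustment.**

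| Reference | Critical value | Power, d = 0.33 | Power, SD 470.7 to 440.5 |
|---|---|---|---|
| Normal, variance known | 1.960 | 88.3% | 86.0% to 90.1% |
| t, 6 df | 2.447 | 74.7% | 71.8% to 77.2% |
| t, 3 df (by pair) | 3.182 | 56.9% | 54.3% to 59.4% |

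Simulating cluster means (200,000 runs) gave the same 74.7% and 56.9%.

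**4. Does it depend on the ICC?** With ICC set to 0, the most favourable case, power at d = 0.33 is still 79% on 6 df. At an assumed ICC of 0.01 it is 62%. The shortfall is mainly a matter of degrees of freedom.

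**5. What pairing could recover.** The 3-df row assumes that pairing removes no variance. Between-subdistrict variance is 0.0024/(0.0024 + 0.9976/51) = 11% of the variance of a subdistrict mean. If pairing removed all of it, SE(d) = √(2 × (0.9976/51)/4) = 0.0989, noncentrality = 3.337 and power on 3 df = 61%.

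**6. Difference detectable with 90% power.** The noncentrality needed is 3.913 (6 df) or 5.014 (3 df).

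- 6 df: 3.913 × 0.1048 × 454.5 ≈ 186 CPM
- 3 df, pairing removing no variance: 5.014 × 0.1048 × 454.5 ≈ 239 CPM

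**7. Uncorrected mixed model.** A simulated balanced REML model with a Wald z test and no small-sample correction gives about 84% power at the pilot ICC. Its type I error is about 4.6% to 4.7% at ICC 0.0024, 6.5% at an assumed 0.01, 8% at an assumed 0.02 and 9.4% at an assumed 0.05.

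**8. Both sexes pooled** (408 per arm, 102 per subdistrict). SE(d) = √(2 × (1 + 101 × 0.0024)/408) = 0.0780; noncentrality = 4.229; power 94% on 6 df and 80% on 3 df.

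**The case against.** **The plan allowed for clustering.** It did: it names four subdistricts per arm and inflates the sample for an ICC. A reader might infer from the shortfall that the cluster design was ignored, and the article does not support that. What is missing is the consequence for inference of having only eight clusters. A design-effect formula with normal quantiles is a familiar planning approximation, but with eight clusters it is a poor one.

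**Degrees of freedom belong in the analysis plan.** Their absence from an article is not a fault, and none is alleged. The point concerns a published figure. An analysis plan that specified cluster-level degrees of freedom would contradict the 90%.

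**The size depends on a test that is not stated.** This stands. An uncorrected Wald test gives about 84%, and at the pilot ICC its type I error is held. A reader might infer that the planned test is anti-conservative. On the article's own ICC it is not; inflation appears only at assumed larger values. Those cannot be ruled out, since the pilot ICC comes from five subdistricts.

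**Nothing commits to a pair-level analysis.** Also correct. Pairing is a feature of the allocation, so 57% is not the power of the plan as written. It is the figure for one possible analysis, under the assumption that pairing removes no variance.

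**Baseline adjustment would help.** Probably, since baseline is measured. But the calculation does not use it and no correlation is given. As an assumption, a correlation of 0.5 acting on the whole variance of the subdistrict means gives 86% (6 df) and 68% (3 df); 0.6 gives 90% and 74%.

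**Conclusion.** The concern holds for the sex-specific comparisons without baseline adjustment. The stated 90% is about 75% on 6 degrees of freedom (72% to 77% over the pilot SDs) and about 84% with an uncorrected Wald-z mixed model. If the randomised pairs are respected, it is about 57% to 61%, depending on how much variance pairing removes. None of these reaches 90%. The small gap between the stated total of 808 and 4 × 204 = 816 changes power by less than one percentage point.

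Two broader conclusions are tempting but not supported. The first is that the whole trial is underpowered: with the sexes pooled, power is about 94% on 6 degrees of freedom. The second is the opposite, that pooling with baseline adjustment restores 90% in every case. Pooling alone gives only 80% on 3 degrees of freedom, and without a stated baseline correlation nothing more can be shown.

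**What to change.** In the sample-size paragraph:

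- Restate the sex-specific power for 150 CPM as about 75% (t reference, 6 degrees of freedom), or keep 90% and restate the detectable difference as about 186 CPM.
- Add that a pair-level analysis (3 degrees of freedom) would have about 57% to 61% power, with a detectable difference of about 239 CPM if pairing removes no variance.

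For the analysis, test the mixed model with small-sample degrees of freedom, such as Kenward-Roger. This guards against type I error inflation if the ICC turns out above the pilot value. If baseline adjustment or pooling is to be credited with extra power, state the assumed correlation and the degrees of freedom.

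The cost is a few sentences and a less favourable stated power. No extra enrolment or data collection is proposed.

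### The sample-size figures do not quite agree: 204 per arm and sex makes 816, not 808; 144 per subdistrict falls just short of both; and 204 fits an effect size of 0.34, not the stated 0.33

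*Protocol article*

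**What the plan says.** All figures but one stand in the sample-size paragraph of the protocol article, section Participant timeline, blinding and sample size.

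- Pilot data: "Mean CPM ranged from 1587.5 (SD 470.7) to 1697.0 (SD 440.5) in the five highly heterogeneous subdistricts (ICC = 0.0024").
- Target effect: "a mean difference of 150 CPM (equivalent to standardized effect size of 0.33) is targeted".
- Design: "Assuming a fixed number of clusters (four intervention, four control").
- Requirement: "204 participants will be needed in each study arm (significance level 5% two-sided, power 90%) summing up to 808 for sex-stratified trial evaluation".
- Recruitment: "Assuming a fixed proportion of 30% for dropouts, 144 participants (72 female, 72 male) are needed in each of the subdistricts at baseline".

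The Outcomes section explains why sex enters the total: "Evaluation of efficacy and possible adverse effects of the PA promotion will be done stratified by sex". The article does not say which SD, formula or software produced 204.

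**The concern.** A reader should be able to go from effect size to number per arm, from there to the total, and from the total to the recruitment target. Here each step breaks slightly. The total is not four times the per-arm figure, the recruitment target is rounded down from that total, and the per-arm figure does not belong to the printed effect size.

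At stake is the recruitment target in all eight subdistricts and the claim of 90% power for the primary outcome within each sex. The paragraph also leaves open which variability was assumed, so the power claim cannot be judged as printed.

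**Working it through.** **Inputs from the article.** Difference 150 CPM; effect size 0.33; quoted SDs 440.5 and 470.7; ICC 0.0024; k = 4 clusters per arm; two-sided 5%; power 90%; dropout 30%; eight subdistricts.

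**Assumptions made here.** 204 is per arm and per sex: two arms alone give 408, nowhere near 808, while the sex-stratified evaluation doubles it. The formula is a normal approximation for a fixed number of clusters.

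**Formula.** The individually randomised size per arm is nI = 2 × (1.960 + 1.2816)² / d². With k clusters per arm, N = nI × k × (1 − ICC) / (k − nI × ICC).

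**Step 1: reproduce 204.** With SD 440.5, d = 150/440.5 = 0.3405.
- nI = 181.2.
- N = 181.2 × 4 × 0.9976 / (4 − 181.2 × 0.0024) = 202.9.
- Per cluster this is 50.7, so 51 whole participants, and 4 × 51 = 204. A noncentral-t version with 2N − 2 degrees of freedom also gives 204.

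**Step 2: the stated effect size.** With d = 0.33:
- nI = 193.0.
- N = 193.0 × 4 × 0.9976 / (4 − 193.0 × 0.0024) = 217.7, so 218 (220 in whole participants per cluster; t version 219).
- Rounding of 0.33 does not explain the gap: d = 0.325 gives 225.4 and d = 0.335 gives 210.5.
- An effect size of 0.33 implies SD 150/0.33 = 454.5, close to the midpoint of the two quoted SDs, (440.5 + 470.7)/2 = 455.6. With SD 470.7, N = 235.7.

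**Step 3: the total.** 204 × 2 arms × 2 sexes = 816. The printed 808 is 4 × 202.

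**Step 4: the baseline target.**
- 808/8 = 101 and 101/0.7 = 144.3, printed as 144.
- From 204: 204/4 = 51 per sex and subdistrict; 51/0.7 = 72.9, so 73 per sex, or 146.
- From 202: 202/4 = 50.5; 50.5/0.7 = 72.1. Rounded up with equal numbers of each sex, this is also 73, or 146.

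**Step 5: what 144 delivers.**
- 144 × 8 × 0.7 = 806.4 evaluable in total, or 72 × 4 × 0.7 = 201.6 per arm and sex.
- Against 808: 1.6 short (0.2%). Against 816: 9.6 short (1.2%).

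**Step 6: power per sex**, with design effect 1 + (N/4 − 1) × 0.0024:

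| Evaluable per arm and sex | d = 0.33 | SD 440.5 | SD 470.7 |
|---|---|---|---|
| 204 | 88.3% | 90.1% | 86.0% |
| 201.6 | 88.0% | 89.8% | 85.7% |

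**The case against.** The strongest defence is that 204 is not a miscalculation. The difference of 150 CPM, SD 440.5, the ICC and four clusters per arm are all printed in the same paragraph, and together they give 204 once each cluster is rounded up to whole participants. On that reading the baseline target misses 90% power by 0.2 points. The 30% dropout is itself a planning guess, and a gap of 0.2% to 1.2% lies well within its uncertainty. The target of 144 follows from 808, so it largely carries one slip forward.

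Most of this stands, and it rules out two stronger readings.

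- A reader might infer that the plan's inputs require 218 and that 204 is simply wrong. The documents do not support that. The printed effect size leads to 218, but a printed SD leads to 204. What is shown is a mismatch between 0.33 and 204, with the SD left unstated.
- A reader might also infer that 816 is certainly right and 808 the misprint. The document does not settle this: 808 = 4 × 202 fits the baseline target better, so 204 could be the slip.

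The defence does not remove the contradictions. No rounding turns 816 into 808, a number described as needed should not be rounded down, and an effect size of 0.34 should not be printed as 0.33. Nor is this detail that an article may leave to a fuller document: the conflicting numbers are all stated.

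**Conclusion.** The point holds as a minor correction. The contradiction between 204 and 808 is exact once 204 is read as per sex. The baseline target leaves 201.6 evaluable per arm and sex, slightly below either requirement. The figure of 204 goes with an effect size of 0.34 (SD 440.5), not with the stated 0.33.

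The shortfall is 1.2% of participants against 816. Power at 201.6 is about 88% if 0.33 is meant and just under 90% if SD 440.5 is meant. If 0.33 at 90% power is the true intention, 201.6 is 7.5% below 218, which is the same loss of about 2 points. None of this endangers the trial or changes its analysis.

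The power figures rest on the normal approximation and on the pilot ICC. They make no allowance for the small number of clusters, which is a separate question from whether the printed figures agree.

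**What to change.** State the SD used in the calculation and print the effect size that belongs to it: 0.34 for SD 440.5, or 0.33 for an SD near 455. Say that the per-arm number is per sex. Then take one of these routes.

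1. **Keep 204 with SD 440.5.** Print 816 as the total and 146 per subdistrict (73 female, 73 male) at baseline. Cost: 146 × 8 − 144 × 8 = 1,168 − 1,152 = 16 more participants, two per subdistrict.
2. **Keep 144.** State 201.6 evaluable per arm and sex (806.4 in total) and restate the power: about 88% at 0.33, or just under 90% at SD 440.5. Name the formula. Cost: none beyond the edit.
3. **Keep 0.33 and 90% power.** Print 218 per arm and sex and 872 in total. The baseline target is then 54.5/0.7 = 77.9, so 78 per sex and 156 per subdistrict. With 55 whole participants per cluster (220 per arm and sex, 880 in total) it is 55/0.7 = 78.6, so 79 per sex and 158. Cost: 12 to 14 more per subdistrict.

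The first two routes need only corrected figures in one paragraph and are the proportionate choice.

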## Discussion

PA is an important component for healthy ageing with many documented benefits both for society and the individual [30]. Thus, the proportion of persons meeting the recommendations for PA should be as high as possible in all age groups. In older adults, PA promotion is especially important, since albeit the potential gain for this group is large, engagement in PA is decreasing with age [31]. Especially outdoor PA, with its added external stimuli is a valuable health resource in older age [32].

In the OUTDOOR ACTIVE intervention trial, we formally evaluate the efficacy of a participatory community-based approach for tailoring an outdoor PA promotion for older adults to a random subdistrict with its given actors and structures. If successful, partners will be sought to implement the intervention in all subdistricts of Bremen such that control subdistricts will also directly benefit from the trial. Moreover, the approach and a ready-to-use toolbox for applying it will be published and made available to other communities. The OUTDOOR ACTIVE intervention trial will provide detailed information on PA intervention for older adults in an urban setting. The use of an objective method for the assessment of the main outcome, physical activity, helps eliminating recall and social desirability bias [33]; and ensures international comparability of the results. Through the participatory nature of the study it will provide valuable insights into drivers and barriers to PA in this group, and it will inform policy makers and other stakeholders how to benefit from the results.

## Abbreviations

AEQUIPA: Physical activity and health equity: primary prevention for healthy ageing
BMBF: Federal ministry of education and research
CBPR: Community-based participatory research
CPM: Counts per minute
CRT: Cluster randomized trial
ICC: Intraclass correlation coefficient
PA: Physical activity
PPM: PRECEDE-PROCEED model
SD: Standard deviation
SES: Socio-economic status
